### Participants

A total of 240 participants will be included. In order for a person to be eligible to participate in the study, the following inclusion criteria have to be met: aged 55–75 years; presence of mild to moderate anxiety symptoms; access to Internet; mastery of the Dutch language; and the possibility and motivation to spend up to 30 min per day on the intervention. Potential individuals that meet any of the following exclusion criteria will be excluded from participation: Alzheimer’s disease or other severe cognitive impairments; unstable severe medical condition(s); severe anxiety or few anxiety symptoms; severe depressive symptomatology; having received psychological or psychopharmacological treatment (with the exception of stable use of benzodiazepines or SSRIs) within the last three months; severe role impairment in at least two areas of role functioning; high suicide risk; substance use disorder or a lifetime diagnosis of bipolar disorder or schizophrenia. The main inclusion criterion—severity of anxiety symptoms—is measured with the GAD-7. This questionnaire uses well-established cut-off points for mild, moderate, and severe anxiety symptoms [48]. These cut-offs point are used to identify our study population: people that score between 5 (cut-off point for mild anxiety) and 15 (cut-off point for severe anxiety) are considered to experience mild to moderately severe anxiety complaints. The information in the participants’ medical record at the general practice is used to determine the presence of a severe unstable medical condition, severe cognitive impairment, and a lifetime diagnosis of bipolar disorder or schizophrenia.. The PHQ-9 [49] is used to assess depressive symptomology (a score of ≥ 20 indicates severe symptoms and excludes people from participation). Role impairment is assessed with the Sheeran Disability Scale (SDS) [50]. A score of ≥ 8 on two of the three subscales is indicative of severe role impairment. Participants are screened for high suicide risk, substance use disorders, and a lifetime diagnosis of bipolar disorder or schizophrenia with the M.I.N.I.-Plus [51].

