### Sample size

Cluster randomization will be applied at the level of the participating mental health counselors. Assuming a mean cluster size of five patients per counselor, an intraclass correlation coefficient of 0.01 [52] and a coefficient of variation of 0.30 [53], 18 mental health counselors in each intervention arm and 90 participants per study arm are needed to detect a between group difference on the GAD-7 with a medium effect size (d = 0.45) with an alpha of 0.05 (two-tailed) and a power of 0.80. Compensating for an anticipated dropout of 25% (based on trials similar to the proposed study with regard to either the treatment approach [40, 54] or the study population [26]), 240 participants will have to be included at baseline. The endpoint for this sample size is 14 weeks. In the most recent and comprehensive Cochrane meta-analysis of 101 studies of media-delivered CBT for anxiety disorders in adults, moderate-quality evidence showed medium effect sizes for CBT compared to control conditions (d = 0.67; 95% confidence interval = 0.55–0.80) [23]. These effects were somewhat smaller than those reported in other recent reviews [17, 19–22] and also smaller than the large effect sizes for Internet-based ACT (0.80 and 0.87) in the study of Fledderus et al. [40] and for Internet-based CBT for anxiety complaints in older adults (1.43) in the study of Dear et al. [26]. These last two studies both compared active treatment to a waiting list control condition. Furthermore, Pots et al. reported an effect size of 0.41 for web-based ACT (with e-mail support) compared to an active control group (expressive writing) [41]. Based on these studies, a moderate effect size of d = 0.45 is estimated for the difference between the ACT online intervention and treatment-as-usual.

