#### Recruitment of participants

A data manager will visit the participating general practices to assist the general practitioner in the selection of patients aged 55–75 years that are eligible to receive an invitation letter for the study. Patients whose medical records mention a lifetime diagnosis of bipolar disorder or schizophrenia, a severe unstable medical condition, Alzheimer’s disease, or other severe cognitive impairments will not receive an invitation. All other patients aged 55–75 years do receive an invitation letter. The invitation letter from the GP to the patients contains information about anxiety complaints and explains the aim, design, and procedure of the study. Furthermore, the letter refers to the study website. On this website, potential participants can read more extensive information about the study and indicate their interest to participate. After doing so, they will be asked to fill in the GAD-7 and PHQ-9 and to indicate whether they have received psychological treatment for emotional problems during the last three months, have Internet access, have sufficient time for treatment, are able to communicate in Dutch, and are aged 55–75 years. If based on these answers patients are still eligible to participate, they are asked if they are willing to be interviewed by phone to determine whether they fulfill all inclusion criteria. They are asked to fill in their telephone number and to indicate on which day they prefer to be called. Within ten days they will be phoned by a research assistant, who will administer the SDS and M.I.N.I.-Plus. Furthermore, they will be asked about their medication use. Patients will also be given the opportunity to ask any remaining questions about the aim of the study and the study procedures. The interviewer will discuss his/her diagnostic findings from the M.I.N.I-Plus with a senior clinical psychologist; subsequently the interviewee is informed by mail about inclusion or exclusion. When patients are eligible, they will receive a link to an online informed consent form and the baseline questionnaires (T0). Ineligible patients will be referred to their general practitioner in case they want help for their complaints. Once eligible patients have filled in the informed consent form and the baseline questionnaires, the mental health counselor at their general practice will be informed about study participation and they will be invited for a first appointment. In addition to the mass mailing, general practitioners and mental health counselors will recommend participation to patients aged 55–75 years that attend the practice with anxiety complaints during the inclusion period. They will inform these patients about the study and refer them to the study website if they want to participate. These patients then follow the screening and inclusion procedure as described above.

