### Primary outcome

#### Anxiety symptom severity

The primary outcome—severity of anxiety symptoms—will be assessed with the GAD-7 [48]. This questionnaire will be used to screen participants on anxiety symptoms and to measure change in these symptoms from baseline to post- and follow-up tests. The primary endpoint for this measure is the measurement 14 weeks after baseline (T1). The GAD-7 consists of seven items that are rated on a 4-point scale ranging from 0 (not at all) to 3 (nearly every day), e.g. “Over the last 2 weeks, how often have you been bothered by: feeling nervous, anxious or on edge.” Higher scores indicate more anxiety symptoms. Total scores are in the range of 0–21 and scores of 5, 10, and 15 are taken as the cut-off points for mild, moderate, and severe anxiety. Psychometric properties of the GAD-7 are adequate and the scale may also be used as a screener for panic disorder, social anxiety, and post-traumatic stress disorder [48, 55, 62]. The reliability and validity of a web-based Dutch translation of the GAD-7 have also been established [63].

Furthermore, during treatment, participants will fill in the GAD-2 [55] several times to measure anxiety symptom severity. The GAD-2 consists of the first two items of the GAD-7, which reflect core anxiety symptoms (“Feeling nervous, anxious, or on edge” and “Not being able to stop or control worrying”). Scores on the GAD-2 will be used in the mediation analyses. The GAD-2 is a reliable, valid, and sufficiently sensitive and specific instrument [55, 63, 64].

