### Statistical analysis

All analyses will use intention-to-treat principles and a two-tailed alpha of 0.05 for significance testing. Cluster randomization at the level of mental health counselors (instead of individual patients) results in a lack of independence for the outcomes of patients receiving treatment from the same counselor. If clustering and dependence of outcome are ignored, this could lead to underestimation of standard errors and regression coefficients [102]. Therefore, multilevel regression analysis will be used to examine the treatment effect on the primary and secondary outcome measures. Multilevel analysis allows modeling of the variability of the outcome measures within clusters and analysis of a repeated-measure design with missing data. In this cluster randomized RCT, three levels can be distinguished: (1) repeated measures within patients; (2) treatment allocation; and (3) mental health counselors. To evaluate the intervention effect, a twofold analysis will be conducted. First, using a mixed-model analysis with treatment as a dummy variable and the dependent variable on baseline as covariate it will be examined whether conditions differ across time. In addition, a subsequent mixed-model analysis without the dependent variable at baseline as covariate will analyze at which particular time point conditions differ as indicated by the interaction effect of treatment × time. Missing data will be imputed using a model-based approach. Covariance will be estimated using an unstructured covariance matrix.

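### Every participant has two pre-treatment GAD-7 and PHQ-9 scores, but the baseline-adjusted model uses only one: a small, free gain in precision is left out

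*Protocol article*

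**What the plan says.** Table 1 of the protocol article marks the GAD-7 and PHQ-9 at screening and, in a separate column, at T0. The section on recruitment of participants shows that these are two occasions. On the study website, "they will be asked to fill in the GAD-7 and PHQ-9". A telephone interview follows within ten days, and only those found eligible get the T0 questionnaires and consent form. Eligibility depends on the screening scores, so every enrolled participant has them. T0 is completed before participants learn which intervention they will receive (Design).

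The section on the primary outcome describes the double use of the scale: "This questionnaire will be used to screen participants on anxiety symptoms and to measure change in these symptoms from baseline" to the later assessments. The primary endpoint is the GAD-7 at T1, 14 weeks after baseline.

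The Statistical analysis section sets out two models. The first tests whether the arms differ across time, "using a mixed-model analysis with treatment as a dummy variable and the dependent variable on baseline as covariate". The second is "a subsequent mixed-model analysis without the dependent variable at baseline as covariate" and uses treatment × time to find the time points at which the arms differ. The screening score appears in neither.

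**The concern.** A single GAD-7 total mixes a person's usual anxiety with error particular to that occasion. If usual anxiety drives the screening, T0 and T1 scores and each has its own error, the screening score tells us something about T1 that T0 does not. Leaving it out then leaves avoidable residual variance in the treatment comparison. The data are already collected and complete among those enrolled, and the Discussion names recruitment as a difficulty, so even a small gain is worth a line in the plan.

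The layout of the two models matters too. As written, time-specific contrasts come from the second model. A covariate added only to the first would not sharpen the T1 contrast, which is the primary endpoint.

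**Working it through.** **1. The plan's own sample size.** Inputs from the Sample size section: d = 0.45, two-sided alpha 0.05, power 0.80, mean cluster size 5, ICC 0.01, coefficient of variation 0.30 (read as that of cluster size), 25% dropout.
- Individual randomization: 2(1.960 + 0.842)² / 0.45² = 77.5 per arm.
- Design effect: 1 + ((1 + 0.30²) × 5 − 1) × 0.01 = 1.0445, giving 77.5 × 1.0445 = 81 per arm, or 17 clusters of 5.
- With a t-test on 2k − 2 cluster degrees of freedom, k = 17 gives power 0.795 and k = 18 gives 0.818. Hence 18 counselors and 90 participants per arm.
- 180 / 0.75 = 240 enrolled.

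The stated size reproduces and takes no credit for any baseline adjustment.

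**2. Formula for the gain.** Let a be the screening-T1 correlation, b the T0-T1 correlation and p the screening-T0 correlation. Adding screening to T0 lowers residual variance by the fraction

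g = (a − pb)² / [(1 − p²)(1 − b²)].

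If a = pb, screening predicts T1 only through T0 and g = 0. The documents give none of these correlations, so all values below are assumptions.

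**3. Sensitivity to the screening-T1 correlation**, ignoring the 5-15 selection, with b = 0.5 and p = 0.8:
- a = 0.50: (0.50 − 0.40)² / (0.36 × 0.75) = 3.7%
- a = 0.45: (0.45 − 0.40)² / (0.36 × 0.75) = 0.9%
- a = 0.40: 0%

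**4. Simulation with selection on a screening score of 5-15.** True score with mean 4 or 8 and SD 4.5; reliability 0.7 to 0.9; T1 true score correlated 0.6 or 0.8 with the pre-treatment one, variance held constant; totals rounded to 0-21.

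| Assumption | Reduction in residual variance |
|---|---|
| Independent errors, stable true score | 1.5-4.7% |
| Error correlation 0.5 between screening and T0 | 1.0-2.8% |
| Error correlation 0.5 and true-score correlation 0.9 between screening and T0 | 0.2-0.9% |

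A simulation that instead sets the correlations directly, with screening and T0 equally predictive of T1 before selection, gave 2.7-6.3%. Its top value needs pre-to-T1 correlations of 0.7 and a screening-T0 correlation of 0.8 before selection.

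**5. Conversion at the rounded upper end, g = 5%.** Standard error: 1 − √0.95 = 2.5%. Completers: 180 / 0.95 − 180 = 9.5, so about 9. In the direct-correlation simulation, power at 90 per arm (normal approximation) was 0.840 with no covariate and 0.881-0.933 with T0 alone. Screening added about one point to the latter.

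**6. Where the T1 contrast comes from.** If the second model's contrast is read as a difference in change from T0, its variance factor is 2(1 − b), against 1 − b² with T0 as a covariate. At b = 0.5 these are 1.00 and 0.75. On that reading, moving the T1 contrast to the adjusted model matters more than the second score does.

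**The case against.** The strongest case against is that nothing here is wrong. Adjusting for the outcome's baseline value is valid, further covariates are often left to an analysis plan that is not shown, and the gain rests on assumed correlations. The GAD-7 asks about the last two weeks and the eligibility call comes within ten days of the web screen. The two recall windows may therefore overlap and the second score may be largely redundant. The change would also give two outcomes a slightly different model from the rest.

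Most of this stands, and it limits the point to an optional improvement with a lower end near zero. It does not remove the point: the article does fix the covariate, and the extra score costs nothing to collect.

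Three stronger readings are tempting, and the documents support none of them.
- A reader might infer that the trial is underpowered without the second score. The sample size reproduces with no baseline adjustment at all.
- A reader might infer that selecting on the screening score biases the comparison through regression to the mean. The same selection rule applies in both arms, and the planned covariate is the later T0 score. Any benefit there is the same variance gain under another name.
- A reader might infer that one added covariate narrows the T1 interval as the plan stands. It would not, because that contrast is assigned to the unadjusted model.

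**Conclusion.** The point holds as a minor efficiency gain. Two pre-treatment scores exist for the GAD-7 and PHQ-9 in every enrolled participant, and the baseline-adjusted model uses one. Under assumed reliabilities and correlations the second is worth roughly 0-5% of residual variance, slightly more only under the most favourable correlations tried. The simulations regress T1 on the pre-treatment scores, without clustering or the T2 and T3 data, so they show the order of size and no more. The planned analysis is valid without the change.

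**What to change.** In the Statistical analysis section, or in the analysis plan before outcome data are seen, state for the GAD-7 and PHQ-9 that the baseline-adjusted mixed model includes both the T0 score and the screening score as covariates. Screening should be added to T0 rather than replace it, because eligibility truncates it. Include treatment × time in that model and take the T1 contrast from it, so that the gain reaches the primary endpoint.

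The cost is one degree of freedom and a model for these two outcomes that differs slightly from the others. No new data are needed, and neither covariate is missing for anyone who completed screening and T0.

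### The powered primary endpoint, GAD-7 at T1, is not tied to the baseline-adjusted model; the only time-point result comes from a treatment × time interaction without the baseline covariate

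*Protocol article*

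**What the plan says.** The article's Primary outcome section, under Anxiety symptom severity, fixes the time point: "The primary endpoint for this measure is the measurement 14 weeks after baseline (T1"). The Sample size section matches it: "The endpoint for this sample size is 14 weeks". That calculation aims "to detect a between group difference on the GAD-7 with a medium effect size (d = 0.45"), at 80% power and a two-sided 5% level. It mentions no baseline adjustment and no baseline-to-T1 correlation.

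The Statistical analysis section then describes a twofold mixed-model analysis.

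- The first model includes treatment as a dummy and "the dependent variable on baseline as covariate it will be examined whether conditions differ across time".
- The second is "a subsequent mixed-model analysis without the dependent variable at baseline as covariate will analyze at which particular time point conditions differ", judged by the treatment × time interaction.

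The section does not mention T1. It does not say which model decides the primary claim, or whether T0 is one of the outcomes in the second model.

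**The concern.** Endpoint and sample size both point to one contrast, the treatment difference in GAD-7 at T1. Neither model is described as the test of that contrast with the baseline value used. The adjusted model asks a different question, about all follow-up visits together. The T1 result has to be read from the unadjusted model, as an interaction with time.

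Two things are at stake. The T1 interaction may be less precise than the data allow, and in part of the plausible range it falls short of the stated 80% power. And if the across-time result is taken as the primary answer, it can disagree with T1 in either direction: it can miss an effect that is present at 14 weeks and fades by month 12, or reach significance through T2 and T3 alone.

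**Working it through.** **Inputs from the Sample size section.** d = 0.45, two-sided alpha 0.05, power 0.80; "Assuming a mean cluster size of five patients per counselor, an intraclass correlation coefficient of 0.01" and "a coefficient of variation of 0.30" (read as variation in cluster size); 18 counselors and 90 patients per arm; 25% dropout; 240 in total.

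**Assumptions, not in the article.** Baseline-to-T1 correlation rho from 0.2 to 0.6. Ratio k of baseline SD to T1 SD of 1, or 0.6 to 0.8. d expressed in T1 SDs. The same design effect for every contrast.

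**Reproducing the stated sample size**

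- Individually randomised: 2 × (1.960 + 0.842)² / 0.45² = 77.5 per arm.
- Design effect: 1 + ((1 + 0.30²) × 5 − 1) × 0.01 = 1.0445.
- 77.5 × 1.0445 = 81.0 per arm, or 16.2 counselors.
- A t test on cluster degrees of freedom gives power 0.769, 0.795 and 0.818 at 16, 17 and 18 counselors per arm, so 18 is the smallest sufficient number, and 18 × 5 = 90.
- Dropout: 180 / (1 − 0.25) = 240.

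The stated figures reproduce for an unadjusted T1 comparison.

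**Power of the two T1 contrasts.** The unadjusted noncentrality is 0.45 × √(90 / (2 × 1.0445)) = 2.95. Divide it by the square root of the variance factor:

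- change from T0: 1 + k² − 2·rho·k, which is 2(1 − rho) at k = 1;
- baseline-adjusted T1: 1 − rho².

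The difference between the factors is (k − rho)², which is never negative. At k = 1 (normal approximation, cluster-df t in brackets):

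| rho | Change factor | Power, change | Adjusted factor | Power, adjusted |
|---|---|---|---|---|
| 0.2 | 1.60 | 0.646 (0.621) | 0.96 | 0.854 (0.834) |
| 0.3 | 1.40 | 0.704 (0.679) | 0.91 | 0.872 (0.853) |
| 0.4 | 1.20 | 0.769 (0.745) | 0.84 | 0.897 (0.879) |
| 0.5 | 1.00 | 0.840 (0.818) | 0.75 | 0.927 (0.912) |
| 0.6 | 0.80 | 0.910 (0.894) | 0.64 | 0.958 (0.948) |

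The change contrast reaches 80% when 2(1 − rho) = (2.95 / 2.80)² = 1.11, so rho = 0.44 (0.48 with cluster df).

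**Allowing for the entry range.** Eligibility limits GAD-7 to 5–15 at entry. This tends to lower rho, but it also lowers the baseline SD, which helps the change contrast. Its power (normal approximation) becomes:

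| k | rho 0.2 | rho 0.3 | rho 0.4 | rho 0.5 | rho needed for 80% |
|---|---|---|---|---|---|
| 0.8 | 0.729 | 0.783 | 0.840 | 0.897 | 0.33 |
| 0.7 | 0.766 | 0.815 | 0.865 | 0.914 | 0.27 |
| 0.6 | 0.797 | 0.840 | 0.883 | 0.923 | 0.21 |

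**What the across-time test sees.** Take the adjusted model averaged equally over T1–T3, with compound symmetry at 0.5. After adjustment each visit has variance 0.75 and each pair covariance 0.25, so the mean has variance (3 × 0.75 + 6 × 0.25) / 9 = 0.417. The standard error is √(0.417 × 2 × 1.0445 / 90) = 0.098.

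| Effect at T1 / T2 / T3 | Mean effect | Power |
|---|---|---|
| 0.45 / 0.45 / 0.45 | 0.45 | 0.996 |
| 0.45 / 0.225 / 0 | 0.225 | 0.63 |
| 0.45 / 0 / 0 | 0.15 | 0.33 |
| 0 / 0.45 / 0.45 | 0.30 | 0.86 |

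The last row has no T1 effect at all.

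**The case against.** The strongest reply is that both models are valid under randomisation, that neither is biased, and that a condensed article may leave exact model terms to an analysis plan. That stands for the details, such as how T0 enters the second model. It does not remove the point: the article does assign single time points to the model without the covariate, and a plan that followed it would carry this forward.

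The power loss also depends on how the model is set up. If the T0 means of the two arms were constrained to be equal, the second model would be about as efficient as the adjusted one. This stands, and it makes the shortfall conditional.

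Three stronger readings are tempting, and the article does not support them.

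- **That leaving out the covariate by itself breaks the planned power.** An unadjusted T1 comparison has 84% power at 90 per arm (82% with cluster df). The loss comes from the change-score form of the interaction.
- **That the trial is underpowered or 240 is wrong.** The sample size reproduces.
- **That two models at 0.05 inflate the type I error.** This needs a rule under which either test can carry the claim. The article states no such rule: it names one primary endpoint, and the two steps read as an overall test followed by locating the difference.

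Finally, averaging equally over T1–T3 is a reading of the across-time question, since the model terms are not given.

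**Conclusion.** The mismatch holds whatever the correlation: the powered primary endpoint is T1, and the plan does not test it in the model that uses the baseline value. If T0 is an outcome with free arm means, the planned T1 contrast is never more efficient than the adjusted one.

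A shortfall against 80% is possible, not shown. It arises only below the break-even correlations derived above, and the article gives neither the correlation nor the SD ratio. The adjusted contrast stays above 80% at every correlation tried. The across-time test does not answer the T1 question, and under the fading patterns shown it would often miss a T1 effect of the planned size.

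This is an improvement available at no cost in data. It is not a demonstrated failure of the design.

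**What to change.** State one primary test: the treatment difference in GAD-7 at T1, two-sided 0.05. Take it from a mixed model with these terms:

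- outcomes: GAD-7 at T1, T2 and T3;
- fixed effects: time, treatment × time (giving a treatment contrast at each visit), T0 GAD-7 and T0 GAD-7 × time;
- random effect: counselor;
- within-patient covariance: unstructured.

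A constrained longitudinal model with a common T0 mean is an equivalent choice. Label the across-time, T2 and T3 contrasts secondary. The model without the baseline covariate may stay as a supportive analysis.

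The cost is wording only. GAD-7 at T0 is already in the assessment schedule, and the sample size does not change. The choice should be recorded before anyone sees outcome data by arm.

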## Methods/design

### Design

The proposed study is a pragmatic cluster single-blind RCT. In a clustered trial, the unit of randomization is not the individual participant, but a group of participants (e.g. patients from one general practice, students from the same school, family members). In this study, randomization takes place on the level of the mental health counselors at general practices, which creates clusters of participants that receive treatment from the same counselor. Cluster randomization is used in this study to reduce experimental contamination [47] and to minimize administrative burden and time spent on training the participating mental health counselors in the used treatment methods. Participating mental health counselors will be randomly assigned to one of the following two conditions: they will either treat all included patients in their practice(s) with the Internet-based ACT intervention or provide all their patients with treatment-as-usual. In most cases, randomization of the mental health counselor will coincide with randomization of the practice(s) at which he/she is employed, but some practices employ multiple counselors. In these practices, a double randomization procedure will be used. First, the counselors are randomized. Second, when patients of this practice are included in the study, they are randomly allocated to one of the counselors in the practice.

The randomization table (containing 36 cells, block randomized into blocks of four cells) will be created by an independent researcher using *R* software. Participants, mental health counselors, and the main researcher (who serves as the contact person for the mental health counselors) cannot be blind for allocation to conditions. However, participants are not informed on whether the treatment they receive is the experimental or active control intervention. They are told that the study aims to compare two treatment options for people with mild to moderate anxiety complaints. This is considered an ethically sound approach, since treatment-as-usual is delivered as optimized care as usual.

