#### Session Rating Scale

The Session Rating Scale (SRS) [99] will be used to measure the working alliance between the participants and their mental health counselor. The items assess four aspects of the working alliance: the relational bond (the degree to which one feels heard, understood, and respected); the degree to which desired goals and topics of the individual were discussed; an evaluation of the therapist’s approach or method that was used; and an evaluation of how the individual perceives the session overall. Instead of using a visual analogue scale, an 11-point scale will be used to answer each of the four items, with “0” depicting the most negative response and “10” depicting the most positive response. The SRS was shown to have high test–retest and internal consistency reliability, as well as acceptable validity [100, 101]. The SRS will be completed after every face-to-face session.

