To examine moderators of the treatment outcome, longitudinal multi-level regression analysis will be performed. Potential moderators will be entered individually in the model. Interaction effects will be investigated (e.g. time × condition × potential moderator). Bivariate latent difference score models will be used for the mediation analysis. This type of analysis is recommended for repeated measurements and multiple mediators, because they allow for a more dynamic approach to mediation, by assessing changes in multiple variables and their interrelations over time [103–105]. Cost-effectiveness analyses will be conducted in agreement with the CHEERS statement [106] and will be determined by relating the difference in healthcare costs (measured with the TiC-P) to the between-group difference in reliable change on GAD-7 scores (cost-effectiveness analysis) and quality-adjusted life-years (QALYs) gained based on the EQ-5D-5 L using the Dutch tariffs (cost–utility analysis). Productivity losses in paid work will be included in the economic evaluation and measured by assessing work-loss days due to absenteeism and work cutback days (presenteeism) while at work but not feeling well. All cost prices will be indexed for the appropriate reference year (likely to be 2017) but not discounted because the study’s time horizon does not exceed the period of a single year. Stochastic uncertainty in the incremental cost-effectiveness ratios (ICERs) will be handled using non-parametric bootstraps (2500 replications), plotted on the ICER plane and depicted in an ICER acceptability curve. Sensitivity analyses will focus on the friction cost versus human capital method and on main cost-drivers.

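### The mediation models are specified without any provision for counselor clustering, unlike the outcome and moderator analyses; fitted at a single level, they would give treatment-to-mediator standard errors that are too small wherever mediators vary between counselors

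*Protocol article*

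**What the plan says.** All places are in the protocol article.

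- **Design:** "randomization takes place on the level of the mental health counselors at general practices". Participants of one counselor therefore form a cluster that is allocated as a whole.
- **Statistical analysis, opening paragraph:** "If clustering and dependence of outcome are ignored, this could lead to underestimation of standard errors and regression coefficients". Multilevel regression follows from this, and its stated scope is the treatment effect on the primary and secondary outcomes. Counselors are named as one of the levels.
- **Statistical analysis, second paragraph:** moderators get longitudinal multilevel regression. For mediators the model class changes: "Bivariate latent difference score models will be used for the mediation analysis". The reasons given are repeated measurements, several mediators and interest in change over time. Clustering is not mentioned.
- **Session Rating Scale (SRS), under Mediator variables:** the scale "will be used to measure the working alliance between the participants and their mental health counselor". Table 1 schedules it only during the intervention, so it has no pre-treatment value. The same holds for the single-item treatment expectancy and self-efficacy mediators.
- **Sample size:** the only clustering figures are given here: "Assuming a mean cluster size of five patients per counselor", "an intraclass correlation coefficient of 0.01" and "a coefficient of variation of 0.30". They serve the GAD-7 comparison. No ICC is given for any mediator.

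**The concern.** A treatment-to-mediator path compares 18 counselors with 18 counselors. It has the same dependence structure as the outcome comparison for which the article requires a multilevel model. A latent difference score model represents repeated measures within a person. It does not account for the counselor unless a cluster level, robust standard errors or a cluster bootstrap is added. The article names the model, gives its reasons for choosing it and adds none of these. Followed as written, the text allows an analysis of the kind that its own opening paragraph warns against.

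What is at stake is the width of the intervals for treatment-to-mediator paths and, through them, for indirect effects. The Discussion counts the moderation and mediation analyses among the strengths of the study. It expects them to be informative even if both arms improve alike, and to guide which treatment components to strengthen. A path that looks significant because of differences between counselors would misdirect that use.

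**Working it through.** **Inputs.** From Sample size: mean cluster size m = 5, coefficient of variation CV = 0.30 (read as that of cluster size; the article does not say of what), ICC 0.01, d = 0.45, power 0.80, 18 counselors and 90 participants per arm, dropout 25%, 240 in total. From Statistical analysis: "All analyses will use intention-to-treat principles and a two-tailed alpha of 0.05 for significance testing". Assumed: mediator ICCs of 0.05, 0.10 and 0.20.

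**Step 1: reproduce the plan's figure.** Without clustering, d = 0.45 at 80% power needs 78 per arm. The design effect is

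DE = 1 + ((1 + CV²)·m − 1)·ICC = 1 + (1.09 × 5 − 1) × 0.01 = 1.0445.

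Then 78 × 1.0445 = 81.5 per arm. Adding one cluster per arm gives 1 + 81.47/5 = 17.3, rounded up to 18 counselors, and 18 × 5 = 90. Finally 180/0.75 = 240. The plan's figures are reproduced with this design effect, so the same formula is used below.

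**Step 2: a treatment-to-mediator path with clusters ignored.** With m = 5 and CV = 0.30, DE = 1 + 4.45·ICC. The naive standard error is too small by 1 − 1/√DE. A nominal two-sided 5% test has true error 2·(1 − Φ(1.96/√DE)).

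| ICC | DE | SE too small by | True type I error | Simulated |
|---|---|---|---|---|
| 0.01 (plan, outcome) | 1.0445 | 2.2% | 0.055 | 0.057 |
| 0.05 (assumed) | 1.2225 | 9.6% | 0.076 | 0.079 |
| 0.10 (assumed) | 1.445 | 16.8% | 0.103 | 0.105 |
| 0.20 (assumed) | 1.89 | 27.3% | 0.154 | 0.156 |

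The simulation used 18 counselors per arm, mean size 5, CV 0.30 and 20,000 runs per ICC. At the baseline cluster size of 240/36 = 6.67, the formula gives 0.057, 0.087, 0.124 and 0.192.

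**Step 3: how far this carries to an indirect effect.** An indirect effect also needs a mediator-to-outcome path. The check requires both paths to be significant, with no true treatment effect on the mediator, mediator ICC 0.20, 36 counselors of mean size 5 and clustering ignored. The false-positive rate is about 0.8% with no mediator-to-outcome path, about 8% with a coefficient of 0.15, and about 15% to 16% with 0.30. The rates in Step 2 are therefore close to an upper limit for the indirect effect, approached only when the second path is strong.

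**Step 4: level versus change.** If the counselor effect is stable over time, it cancels in a change score. With a level ICC of 0.20 and a stable counselor effect, the single-level test on change ran at about 5%. Inflation therefore requires either that change itself differs between counselors, or that treatment acts on the level of a mediator. The second case is relevant to the SRS, treatment expectancy and self-efficacy, whose first values come after treatment has begun.

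**The case against.** The strongest reply is that the article is silent on clustering here and has not decided against it. A latent difference score model can be fitted with a counselor level or cluster-robust standard errors. The same section begins by saying that patients of one counselor are not independent, and a condensed article may leave the standard-error method to the analysis plan. This stands in part. A reader might infer that the counselor level is deliberately dropped, but the text does not say that the models are single-level. The point remains because the article does fix the mediation model and its rationale, and it states multilevel analysis for outcomes and again for moderators but not here.

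The reply is also right on size. At the article's only ICC the effect is trivial, and the larger figures depend on assumed ICCs. They concern a single path, so the idea that a mediator could be declared on between-counselor variation alone does not hold: a mediator-to-outcome relation is needed as well.

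A reader might also infer that working alliance is the worst case, because patients of one counselor rate the same person. That is plausible but not shown. The article gives no ICC for the SRS, and a stable counselor effect would cancel in change scores.

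Finally, some process measures (AAQ-II, CERQ, FFMQ-SF) are listed as secondary outcomes, so treatment effects on them already fall under the multilevel analysis.

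**Conclusion.** The concern holds in a conditional and limited form. The mediation analysis is specified without provision for counselor clustering, which is out of line with the unit of randomization, with the article's own warning and with its other analyses. If it is fitted at a single level, the understatement is negligible should mediators cluster as little as the outcome is assumed to. It becomes material, with standard errors about 10% to 27% too small and type I error of about 0.08 to 0.15 for the treatment-to-mediator path, if mediator ICCs lie between 0.05 and 0.20. That range is an assumption. The result also rests on reading the coefficient of variation as that of cluster size, and on counselors differing in mediator change or in the level of mediators without a pre-treatment value. The primary GAD-7 analysis and the multilevel secondary and moderator analyses are unaffected.

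**What to change.** Add one sentence to the mediation text in Statistical analysis. It should say that all latent difference score models take counselor as the cluster variable with cluster-robust standard errors, or that intervals for indirect effects come from a bootstrap that resamples whole counselors within each arm. With only 36 counselors the bootstrap is preferable, because cluster-robust standard errors are less dependable with few clusters and many parameters. If robust standard errors are used, keep the number of model parameters low.

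The change needs no new data and no change to the design: one sentence, and a cluster option or resampling loop in the software. The downside is somewhat wider mediation intervals.
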